**Methods:**

This study is a randomized, double-blind, controlled trial. Forty-eight individuals aged 20 to 55 years with cLBP will be randomly assigned to receive either (1) a 3-week DLPFC-tDCS intervention (*n* = 24) or (2) a 3-week M1-tDCS intervention (*n* = 24), administered four times per week for a total of 12 sessions. Clinical outcomes will be assessed at baseline, 3 weeks, and 6 and 12 months after randomization. Primary outcomes include pain intensity, disability, and scores on the Hamilton Depression and Hamilton Anxiety scales. Secondary outcomes include surface electromyography characteristics of trunk muscles, oxygenated and deoxygenated hemoglobin concentrations in the M1 and DLPFC, and functional connectivity between these two brain regions. These outcomes will be evaluated before and after the intervention. Effect sizes and a mixed-model repeated measures analysis of variance (2 groups × 4 time points) will be calculated.

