### Study design

2.1

This randomized, double-blind, controlled trial will be conducted at the Department of Rehabilitation Medicine, First Affiliated Hospital, Sun Yat-sen University, China. The trial will follow a blinded design in which assessors, therapists, and participants remain unaware of group assignments. Participants will be randomly assigned to one of two groups: (1) the Study Group receiving DLPFC-tDCS and (2) the Control Group receiving M1-tDCS. Assessments will be performed at baseline, 3 weeks, 6 months, and 12 months post-randomization, with the primary outcome evaluation occurring at 3 weeks. The study will be reported in accordance with CONSORT guidelines. The experimental flowchart is illustrated in Figure 1.

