#### Sample size

2.5.3

Based on the following formula and our preliminary experimental results of the primary outcome measures (VAS), with a significance level of *α* = 0.05, test power (1-*β*) = 0.9, a mean difference of 1.15, and a variance index of 1.48, it was determined that 20 participants per group are required. To account for an estimated attrition rate of 120%, a total of 48 cLBP participants will be recruited. To compare the effects after the intervention of the two groups, twenty-four right-handed healthy individuals with no history of cLBP were recruited.

$$N={\left[\frac{(t_{\alpha ∕2}+t_{\beta })S}{\delta }\right]}^{2}$$

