#### Statistical analysis

2.11.1

Statistical analyses will be performed using SPSS (version 25.0, IBM, USA). Before performing descriptive statistics, the Shapiro–Wilk test will be applied to evaluate the normality of data distribution. Data following a normal distribution will be reported as mean and standard deviation (SD), while non-normally distributed data will be expressed as medians with interquartile range (IQR). Categorical variables will be summarized as percentages and frequencies. Baseline demographic and clinical characteristics will be compared between groups using appropriate statistical tests based on the data type. Continuous variables that follow normal distribution will be analyzed while using independent sample *t*-tests, whereas non-parametric Mann–Whitney *U*-tests will be applied for non-normally distributed continuous data. Categorical variables will be analyzed using chi-square tests or Fisher’s exact tests, as appropriate. Correlations between variables will be evaluated using the Pearson correlation coefficient or Spearman correlation coefficient based on the type of data. A repeated-measures analysis of variance (2 groups × 4 time points) will be performed to assess the therapeutic effects on primary and secondary outcomes. If a significant main effect was observed, *post hoc* tests with Bonferroni correction were conducted. A *p*-value of <0.05 will be considered statistically significant.

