### Data collection, management, and monitoring

2.12

Data collection will be performed by experienced attending physicians, therapists, and researchers who are independent of the treatment allocation and intervention procedures. All collected data will be promptly recorded in designated case report forms (CRFs). A designated researcher will digitize the data while ensuring patient privacy and data security through unique identifiers. Two data managers, who will remain blinded to group assignments, will independently process the completed CRFs and enter the data into an Excel database. To maintain data integrity, both data managers will undergo comprehensive training in data monitoring and entry procedures.

To reduce the probability of an adverse event, the participants will be rigorously screened in accordance with the exclusion and inclusion criteria. Adverse effects and events will be closely monitored during the clinical trial. If this occurs, it will be noted in the CRF. Some incidents will be monitored, and when these incidents are inappropriate, the treatment will be discontinued, such as exacerbation of the condition, serious adverse events, poor adherence leading to a loss of follow-up or the development of a new serious illness affecting the course of this protocol.

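### Read as a classical ANOVA, the four-visit analysis drops a participant's observed 3-week result from the primary comparison whenever a later visit is missed

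*Protocol article*

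**What the plan says.** Section 2.11.1 names one method for treatment effects, to be run in SPSS version 25: "A repeated-measures analysis of variance (2 groups × 4 time points) will be performed to assess the therapeutic effects on primary and secondary outcomes". Group comparisons at single time points are left to Bonferroni-corrected post hoc tests. No separate 3-week analysis is named.

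The abstract labels the analysis differently: "Effect sizes and a mixed-model repeated measures analysis of variance (2 groups × 4 time points) will be calculated".

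Section 2.1 gives the visit schedule, "Assessments will be performed at baseline, 3 weeks, 6 months, and 12 months post-randomization", and continues "with the primary outcome evaluation occurring at 3 weeks". The decisive visit is therefore the second of four, and two later visits follow over the rest of a year.

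Section 2.5.3 expects losses: it calculates 20 per group and recruits 48 in total. Section 2.12 lists reasons for which "the treatment will be discontinued, such as exacerbation of the condition, serious adverse events, poor adherence leading to a loss of follow-up". Section 2.9 describes telephone contact and reminders for missed assessments.

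**The concern.** A classical repeated-measures ANOVA needs a complete row of measurements for each participant, and the SPSS repeated-measures procedure deletes listwise. Missing the 6- or 12-month visit therefore removes the whole participant, including a 3-week value already collected. The primary comparison then depends on attendance up to a year after the decisive measurement.

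Two things are at stake. The first is precision: in a trial of 48, each discarded 3-week value matters. The second is possible bias: if people who are worse at 3 weeks are less likely to return later, those with all four visits are a selected group at 3 weeks.

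This is not a complaint that a missing-data section is absent. The protocol names a specific method, and the classical form of that method fits poorly with the protocol's own primary time point.

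**Working it through.** **1. The plan's own figure.** Section 2.5.3 works "with a significance level of *α* = 0.05, test power (1-*β*) = 0.9", with difference δ = 1.15 and spread S = 1.48, in N = [(t_α/2 + t_β)S/δ]².
- Normal quantiles: [(1.960 + 1.282) × 1.48/1.15]² = 17.4.
- The same formula iterated with t quantiles: 19.4, rounded up to 20. The stated 20 per group is reproduced.
- 20 × 1.2 = 24 per group, and 2 × 24 = 48. The printed attrition figure of 120% is read here as this multiplier.

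The formula is a one-sample or paired form. That is a separate matter; the power figures below use the two-sample comparison that the trial will make.

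**2. Values discarded.** The planned loss is 24 − 20 = 4 per arm, or 8 of 48 (16.7%). If all of it falls after week 3, all 48 have a 3-week value and a complete-case ANOVA uses 40 of them.

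**3. Precision.** The standard error of the difference is S√(2/n).
- n = 24: 1.48 × √(2/24) = 0.427.
- n = 20: 1.48 × √(2/20) = 0.468.
- Ratio: √(24/20) = 1.095, about 10% larger.

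**4. Power.** Two-sided two-sample t test, α = 0.05, noncentrality 1.15/SE, 2n − 2 degrees of freedom. The document calls 1.48 a variance index, so both readings are shown.

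| Reading of 1.48 | n = 24 per arm | n = 20 per arm |
|---|---|---|
| SD = 1.48 | 1.15/0.427 = 2.69; power 75% | 1.15/0.468 = 2.46; power 67% |
| Variance = 1.48 (SD 1.217) | 1.15/0.351 = 3.27; power 89% | 1.15/0.385 = 2.99; power 83% |

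**5. Possible bias (illustrative).** Simulation with these assumptions, none of which comes from the protocol: everyone is measured at 3 weeks; later dropout follows a logistic function of the 3-week VAS, with the same rule in both arms; overall loss is 17% or 30%; SD is 1.48. The entries are complete-case group differences at 3 weeks.

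| True difference | Slope per SD | 17% lost | 30% lost |
|---|---|---|---|
| 1.15 | 0 (unrelated to outcome) | 1.15 | 1.15 |
| 1.15 | 0.7 | 1.08 | 1.05 |
| 1.15 | 1.5 | 0.96 | 0.89 |
| 0 | any of these | about 0 | about 0 |

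With a true effect, one common rule removes more people from the arm that is doing worse, so the difference shrinks. With no true effect and the same rule in both arms, the group difference is not biased. In this setting every 3-week value exists, so an analysis that uses them all does not have this bias.

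**The case against.** **Listwise deletion is not stated.** This is true. The abstract's label could mean a likelihood-based mixed model that keeps partial data, and SPSS offers both. Post hoc tests run outside the ANOVA could also use all 3-week values. However, a mixed ANOVA with a 2 × 4 layout commonly means the between-within form, which deletes listwise, and section 2.11.1 drops the mixed-model label altogether. The ambiguity stands and needs resolving.

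**The loss is already planned for.** Recruiting 24 to keep 20 does anticipate it. Even so, an allowance for people who cannot be measured is no reason to discard people who were measured at the primary time point.

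**An unseen analysis plan may cover this.** It may well define analysis sets and missing-data rules, and their absence here is no finding. The point rests on the method that the protocol does name.

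**The stronger reading.** A reader might infer from section 2.12 that participants who worsen are removed, so that the 3-week comparison covers only those who did well enough to remain for 12 months. The document does not support that. The section stops treatment, which lasts 3 weeks; it does not end follow-up or exclude data. Section 2.9 makes no exception for people who have stopped. The only listed reason tied to loss of follow-up is poor adherence; exacerbation is listed separately. Late dropout could be unrelated to outcome or could include people who improved.

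A reader might also infer an inflated false-positive rate. That requires strongly unequal loss between arms: assuming 80% against 20% of worsened participants lost gives a spurious difference of about 0.27 and a type I error of about 9.5%. Nothing in the protocol supports such an imbalance. Both arms receive active stimulation plus the same exercise, and participants are blinded.

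**Conclusion.** The point holds in a limited form. Under the classical reading of section 2.11.1, the primary 3-week comparison discards 3-week data from anyone who misses a later visit. The abstract's label does not clearly displace that reading.

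If the whole planned loss falls after week 3, the cost is 8 of 48 observed values, a standard error about 10% larger, and a fall in power from about 75% to 67% (89% to 83% if 1.48 is a variance). This is an upper figure for the planned loss: anyone lost before week 3 has no 3-week value to save under any method.

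Bias is a possibility, not a demonstrated result. At the planned loss of about 17%, the assumed dropout rules shrink a true 1.15 to between 0.96 and 1.08. There is no bias when dropout is unrelated to outcome, or when there is no true effect and loss is equal in both arms.

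The conclusion concerns the primary outcomes. For the secondary outcomes the abstract says "These outcomes will be evaluated before and after the intervention", so a four-visit layout does not describe them.

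**What to change.** **Section 2.11.1 and the abstract.** Give the same method in both places: a likelihood-based linear mixed model (the MIXED procedure in SPSS) of all randomised participants, analysed as allocated. Include group, visit and their interaction, and use every available visit. Name the group contrast at 3 weeks as the primary comparison, with the 6- and 12-month contrasts as follow-up results.

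**Section 2.12, as a clarification of wording.** Separate stopping treatment from loss to follow-up, and state that participants who stop treatment continue the scheduled assessments unless they withdraw consent to them. This leaves the clinical reasons for stopping as they are.

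**Cost.** No new visits and no change to the sample size. There is slightly more modelling work than for the ANOVA, and some follow-up effort for participants who are off treatment.

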### Data collection

2.9

A blinded researcher will gather outcome data before randomization (baseline), post-intervention (3 weeks post-randomization), and during follow-up evaluations at 6 and 12 months after the intervention. Assessments will be conducted again at the post-intervention stage to evaluate immediate effects and during follow-up to assess both short- and long-term intervention outcomes. All data will be systematically documented and stored in the trial database throughout the study. Furthermore, participants will be contacted by a designated researcher *via* telephone for follow-up. If a participant fails to complete the scheduled evaluation within 2 days of the appointment, they will receive a reminder message or a follow-up call from the research team.

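### The 2 × 4 ANOVA counts the pre-randomization baseline as an outcome visit and never adjusts for it, so the 3-week comparison gives up precision

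*Protocol article*

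**What the plan says.** Section 2.1 (Study design) fixes the visits and the primary time point: "Assessments will be performed at baseline, 3 weeks, 6 months, and 12 months post-randomization, with the primary outcome evaluation occurring at 3 weeks". Section 2.9 (Data collection) places baseline ahead of allocation: "A blinded researcher will gather outcome data before randomization (baseline".

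The efficacy model is given twice. Section 2.11.1 (Statistical analysis) says "A repeated-measures analysis of variance (2 groups × 4 time points) will be performed to assess the therapeutic effects on primary and secondary outcomes", and the Methods part of the abstract says "a mixed-model repeated measures analysis of variance (2 groups × 4 time points) will be calculated". With four assessments and four levels of time, baseline has to be one of the levels.

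The only other use of baseline is in section 2.11.1: "Baseline demographic and clinical characteristics will be compared between groups using appropriate statistical tests based on the data type". No section names a baseline covariate, an ANCOVA or a model with a common baseline mean. On follow-up tests, section 2.11.1 says "If a significant main effect was observed, *post hoc* tests with Bonferroni correction were conducted"; it does not say which 3-week contrast will be reported.

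The abstract has the secondary outcomes (sEMG, fNIRS) evaluated before and after the intervention, yet section 2.11.1 sends them to the same four-level model.

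**The concern.** A value taken before randomization can differ between the arms only by chance. It carries no treatment effect, but it does carry information about each patient's later score. Placed in the response vector, it can enter a 3-week treatment contrast in only two ways. It is ignored (the raw 3-week difference), or it is subtracted in full (the change from baseline, which is the group × time contrast between those two visits). Neither uses the weight that the data support.

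Precision is at stake in a trial of 48 patients, as is the influence of whatever baseline imbalance happens to occur. Allocation in section 2.6 ranks random numbers without stratification, so nothing in the design limits that imbalance. The baseline tests in section 2.11.1 do not feed into the treatment estimate. The point holds with complete data and with a clearly named 3-week contrast.

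**Working it through.** **Inputs from section 2.5.3 (Sample size), VAS.** Difference 1.15; S = 1.48; "a significance level of *α* = 0.05", two-sided because the formula uses α/2; power 0.9; 20 per group, 48 in total.

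**The plan's own figure.** The printed formula N = [(tα/2 + tβ)S/δ]² gives 17.4 with normal quantiles and 20 with iterated t quantiles on n − 1 degrees of freedom. Then 20 × 1.2 = 24 per group. The 20 reproduces only if 1.48 is an SD; read as a variance it gives 11.8, or 12. I therefore take 1.48 as the 3-week SD.

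**Assumptions not in the documents.** The baseline-to-3-week correlation r is set at 0.3, 0.5 and 0.7. The baseline SD, S0, is set first at 1.48 (equal SDs). It is then set at 0.87, which is a uniform spread over the VAS 4–7 entry range: 3/√12 = 0.87.

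**Per-patient error variance at 3 weeks, with S1 the 3-week SD.**
- Raw: S1²
- Change: S1² + S0² − 2r·S1·S0
- Baseline-adjusted: S1²(1 − r²)

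Raw minus adjusted is r²S1². Change minus adjusted is (S0 − r·S1)². Neither can be negative, so adjustment never has the larger variance, whatever the SDs. With equal SDs, adjusted/change = (1 + r)/2, a saving of 35%, 25% and 15% at r = 0.3, 0.5 and 0.7. The saving over raw is r²: 9%, 25% and 49%.

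**Power at 24 per arm** (noncentral t, 46 degrees of freedom, 45 with the covariate; SE = SD × √(2/24)):

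| r | Raw | Change, S0 = 1.48 | Change, S0 = 0.87 | Adjusted |
|---|---|---|---|---|
| 0.3 | 75% | 61% | 75% | 79% |
| 0.5 | 75% | 75% | 86% | 86% |
| 0.7 | 75% | 93% | 95% | 96% |

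Raw and adjusted power do not depend on S0. At 20 per arm with equal SDs, raw has 67%, change 53%/67%/87% and adjusted 71%/79%/92%. With S0 = 0.87 the variance saved over change is only 8%/1%/2%; with S0 = 1.0 it is 13%/4%/0%.

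**Imbalance.** With SD 1.48 and 24 per arm, the chance baseline difference has SE 1.48 × √(2/24) = 0.43 cm, a 95% range of about ±0.84 cm. Take an imbalance of 0.5 baseline SD: t = 0.5/√(2/24) = 1.73 on 46 degrees of freedom, p = 0.09. Given that imbalance:
- Raw shifts by 0.5·r·S1. At r = 0.5 this is 0.5 × 0.5 × 1.48 = +0.37 cm, or 32% of 1.15.
- Change shifts by 0.5·(r·S1 − S0). At r = 0.5 this is 0.5 × (0.74 − 1.48) = −0.37 cm with equal SDs, and 0.5 × (0.74 − 0.87), about −0.07 cm, with S0 = 0.87.
- Adjusted shifts by about 0.

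**Simulation check** (20,000 trials, 24 per arm, r = 0.5, equal SDs). The SDs of the estimates were 0.430 raw, 0.424 change and 0.375 adjusted. The slopes on the observed imbalance were +0.51, −0.49 and +0.02. The adjusted 0.375 lies slightly above the formula's 0.370 because the baseline slope is estimated.

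**The case against.** The strongest case on the other side has four parts.

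**The model is conventional and valid.** This stands. Under randomization both ANOVA contrasts are unbiased on average and type I error is kept. A reader might infer that the 3-week answer is biased; the documents do not support that. The 0.37 cm shift is conditional on a particular imbalance, itself a 1.73-SE event.

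**The gain over change rests on equal SDs.** This also stands. A reader might infer a 15–35% saving at every plausible correlation. Section 2.5.1 admits patients with VAS 4–7 at least once in the past week. That does not cap the baseline score, but it plausibly narrows its spread, and with S0 between 0.87 and 1.0 the saving over change falls to about 0–13%.

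**The comparator is not fixed.** Section 2.11.1 does not name the contrast. Quoting change alone would exaggerate the loss at low r: at r = 0.3 adjustment gains 18 points over change (61% to 79%) with equal SDs, but 4 points over raw (75% to 79%). Hence both are shown. Nor does imbalance push both contrasts the same way: with equal SDs raw follows it and change over-corrects.

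**Covariates are commonly left to an analysis plan.** This does not remove the point. The model with baseline as a response level is stated in the article, twice; the criticism is of that stated choice and not of a missing detail.

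A reader might also infer that the baseline tests are meant to justify leaving out adjustment. Section 2.11.1 does not say so.

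**Conclusion.** The point holds as a loss of efficiency in a model that the article states, and should be corrected; it is not an error of validity. That adjustment has no larger error variance than either ANOVA contrast is certain, apart from the degree of freedom spent and the small cost of estimating the slope. How much is lost is uncertain, because neither r nor the baseline SD is in the documents.

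Across r = 0.3 to 0.7 at 24 per arm, the gain in power is 4 to 21 points over the raw contrast. Over change it is 18 to 3 points with equal SDs, and 4 points or fewer if the baseline SD is near 0.87. The figures assume complete 3-week data on all 48 patients and 1.48 as the 3-week SD. The raw contrast has 75% power against a 90% target because the printed formula is the one-sample form. That is a separate matter, but it makes recoverable precision worth more here.

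**What to change.** Take baseline out of the response vector. For each primary outcome, model the 3-week, 6-month and 12-month values with arm, visit, arm × visit, baseline value and baseline × visit. Report the arm difference at 3 weeks with a 95% CI.

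For outcomes measured only before and after the intervention (sEMG, fNIRS), use ANCOVA of the post-intervention value on arm and baseline value.

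Describing baseline without significance tests is optional tidying; it changes no treatment estimate.

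The cost is a paragraph of analysis wording and one degree of freedom per baseline covariate. No new data are needed.

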This study primarily aims to assess the role of M1-DLPFC functional connectivity in regulating trunk muscle synergy patterns in cLBP patients. The primary hypothesis proposes that abnormal trunk muscle synergy in cLBP is associated with reduced M1-DLPFC functional connectivity. The secondary objective is to evaluate the effects of M1-tDCS and DLPFC-tDCS post-intervention and at follow-up in terms of (1) pain, (2) disability, (3) mental health, (4) surface electromyography characteristics of trunk muscles, and (5) the concentration of oxygenated and deoxygenated hemoglobin in the cerebral cortex of M1 and DLPFC. The secondary hypothesis is that DLPFC-tDCS is more effective than M1-tDCS in increasing M1-DLPFC functional connectivity and improving symptoms of depression and anxiety.

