**Figure 3 fig3:**
[figure not shown]
Electrode position of DLPFC-tDCS group **(A)** and M1-tDCS group **(B)**.

For the M1-tDCS group, the anode will be placed on the contralateral side of the most painful region, while four cathodes will be positioned at a 3.5 cm radius around C3/C4 (Figure 3B). The stimulation intensity will be gradually increased to 2 mA over the first 30 s, with a total intervention duration of 20 min per session. Each patient will undergo tDCS treatment once per day, 4 days a week, for 3 weeks.

In addition to tDCS, all participants will undergo a sling exercise program. Evaluations will be performed in four positions: prone lumbar setting, supine lumbar setting, side-lying hip abduction setting, and side-lying hip adduction setting, with weak muscle chains identified (2–3 per participant). Following the principle of progressive training, sling exercise postures—including prone bridging, supine pelvic lift, side-lying hip adduction, and side-lying hip abduction —will gradually increase in difficulty while reducing external support (as detailed in Table 1). Participants will not take analgesics or undergo any other treatments during the intervention. No pain or discomfort is expected during the sessions. The sling exercise program will be supervised by a physiotherapist with over 5 years of clinical experience. The treatment will be given once daily, 4 days per week, for 3 weeks, with 12 sessions in total.

**Table 1 tab1:** Description of sling exercise protocol.

Exercise	Exercise set up	Instruction to individual
Supine pelvic lift	Individual supine with arms parallel to body; one leg flexed with knee at 90 degree and foot on surface; narrow sling at flexed knee; Wide sling under pelvis, attached with elastic cords.	Extend knee in sling; bring another leg up parallel to other; Lift a leveled pelvis up to a straight body position.
Prone bridging	Individual prone with upper body supported on forearms; elbows directly under shoulders; narrow sling just below knee; wide sling under abdomen, attached with elastic cords.	Lift another leg from surface; lift a leveled pelvis up to a straight body position.
Side-lying hip abduction	Individual side-lying with upper body supported on shoulder; top arm parallel to body; narrow sling at knee of bottom leg; wide sling under hip, attached with elastic cords.	Lift top leg; extend bottom hip; lift up to a straight body position by pressing bottom leg into sling.

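### Post hoc tests are gated on an unspecified main effect, and neither the group-by-time interaction nor a 3-week contrast between arms is named

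*Protocol article*

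**What the plan says.** Section 2.11.1 (Statistical analysis) gives one model: "A repeated-measures analysis of variance (2 groups × 4 time points) will be performed to assess the therapeutic effects on primary and secondary outcomes". It gives one decision rule, that Bonferroni-corrected post hoc tests are run "If a significant main effect was observed". The abstract repeats the model without naming a term or contrast: "Effect sizes and a mixed-model repeated measures analysis of variance (2 groups × 4 time points) will be calculated".

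The t-tests and Mann–Whitney tests in Section 2.11.1 follow the sentence on comparing baseline characteristics and are not assigned to any outcome at 3 weeks.

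Three other places bear on the rule:

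- Section 2.1 (Study design) lists four assessments, "with the primary outcome evaluation occurring at 3 weeks".
- The Introduction frames the treatment question as a comparison between arms. Its secondary hypothesis is that "DLPFC-tDCS is more effective than M1-tDCS in increasing M1-DLPFC functional connectivity and improving symptoms of depression and anxiety".
- Section 2.8 (Intervention) gives both arms an active co-treatment: "In addition to tDCS, all participants will undergo a sling exercise program".

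**The concern.** A group-by-time ANOVA has two main effects and an interaction. With a baseline visit among the four time points, the treatment effect shows up mainly in the interaction or in a contrast at a named visit. The article instead refers to a main effect and leaves open which one.

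- **Time main effect.** It pools the arms and asks whether scores change over the year. It cannot distinguish DLPFC-tDCS from M1-tDCS.
- **Group main effect.** It averages the difference between arms over all four visits. Section 2.9 collects baseline before randomisation, so the expected difference at that visit is zero and pulls the average down.

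At stake is whether the comparison at the declared primary time has a clearly named test, and whether a real 3-week difference could be left untested because a diluted term missed significance. Leaving the gating term open also allows it to be chosen after the results are known.

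**Working it through.** **Inputs from the article.** Section 2.5.3 sizes the trial on VAS "with a significance level of *α* = 0.05, test power (1-*β*) = 0.9", with a mean difference of 1.15, a variance index of 1.48, 20 per group, and 48 in total. Section 2.6 allocates 24 per arm.

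**The article's own figure.** The printed formula with normal quantiles gives [(1.960 + 1.282) × 1.48 / 1.15]² = 17.4. With iterated t quantiles (df n − 1) it gives 19.4, so 20. Then 20 × 1.2 = 24 per arm and 48 in total. The figure reproduces when 1.48 is read as an SD, and that reading is used below. It does not bear on the gating rule.

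**Assumptions not in the article.** 1.48 is the SD at each visit. 1.15 is the difference between arms at 3 weeks. Any two visits within a person correlate at a common ρ of 0.3, 0.5 or 0.7. The effect trajectories and the shared improvement are also assumed. All 24 per arm are analysed, two-sided at 0.05.

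**Dilution of the group main effect.**

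- 3 weeks only (0, 1.15, 0, 0): mean 1.15 / 4 = 0.2875, or 0.25 of the effect.
- Sustained (0, 1.15, 1.15, 1.15): mean 3 × 1.15 / 4 = 0.8625, or 0.75 of the effect.
- Fading (full at 3 weeks, half at 6 months, a quarter at 12 months): mean 1.15 × 1.75 / 4 = 0.503.

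**Standard errors**

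- Group main effect: 1.48 × √((1 + 3ρ)/4) × √(2/24) = 0.294, 0.338, 0.376 for ρ = 0.3, 0.5, 0.7.
- Plain 3-week difference: 1.48 × √(2/24) = 0.427.
- Baseline-adjusted 3-week difference: 0.427 × √(1 − ρ²) = 0.408, 0.370, 0.305.

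At ρ = 0.5 with a 3-week-only effect, the noncentrality of the group main effect is 0.2875 / 0.338 = 0.85, which gives 13% power. For the plain t-test it is 1.15 / 0.427 = 2.69, which gives 75%.

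**Interaction.** Noncentrality is (24/2) × Σ(dⱼ − d̄)² / [1.48² × (1 − ρ)], where dⱼ is the difference between arms at visit j, with 3 and 138 df. For both the 3-week-only and the sustained pattern, Σ(dⱼ − d̄)² = 0.75 × 1.15² = 0.992. At ρ = 0.5 this gives 10.9 and 79% power.

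**Power (noncentral t and F)**

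| Test | ρ = 0.3 | ρ = 0.5 | ρ = 0.7 |
|---|---|---|---|
| Group main effect, 3 weeks only | 16% | 13% | 12% |
| Group main effect, fading | 39% | 31% | 26% |
| Group main effect, sustained | 82% | 71% | 61% |
| Interaction, 3 weeks only or sustained | 63% | 79% | 95% |
| Interaction, fading | 48% | 64% | 87% |
| 3-week t-test, any pattern | 75% | 75% | 75% |
| 3-week baseline-adjusted, any pattern | 79% | 86% | 96% |

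**Time main effect with no difference between arms.** Suppose both arms improve by 1 point from 3 weeks on. The noncentrality is 48 × 0.75 / [1.48² × (1 − ρ)] = 23.5 at ρ = 0.3 and 32.9 at ρ = 0.5. The time effect is then significant in about 99% or more of trials. A shared improvement of 2 points makes it practically certain.

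**The case against.** A reader might infer that the plan never tests the interaction or the 3-week difference. The article does not support that. A two-factor ANOVA of this kind normally yields the interaction F test, nothing excludes it, and the unspecified post hoc tests could include the two arms at 3 weeks. What can be said is that neither is named, and that a 3-week comparison reached through the post hoc tests would sit behind the gate.

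A reader might also infer that the rule both opens when treatment does nothing and closes on a real effect. These belong to different readings. If either main effect suffices, the time effect keeps the gate open and a weak group effect blocks nothing. If only the group effect counts, the gate is a diluted test of treatment, but still a test of it. For a sustained effect at ρ = 0.3 its 82% even slightly exceeds the 79% of the adjusted 3-week comparison. Nor is an inflated false-positive rate shown: an open gate only admits Bonferroni-corrected comparisons.

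The sizes depend on assumed correlations and trajectories, and the lowest figures belong to the most extreme trajectory. Entering baseline as a response is common practice; adjusting for it is a gain in precision, not the correction of an error.

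Finally, model terms and contrasts are often left to an analysis plan. That would answer silence, but the article states a decision rule, and that rule does not match its own primary time point.

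**Conclusion.** The concern holds in this limited form. The only stated decision rule rests on an unspecified main effect, and the article names neither the interaction nor a 3-week contrast between arms, although it places the primary evaluation at 3 weeks.

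Read as the time effect, or as either effect, the gate tells nothing about treatment and almost always opens if both arms improve. Read as the group effect, it tests 0.25 to 0.75 of the 3-week effect under the patterns considered. Its power is then about 12–16% for a 3-week-only effect and 61–82% for a sustained one.

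The exact percentages rest on the assumptions listed above. For a 3-week-only effect, the disadvantage of the group main effect against a direct 3-week comparison holds over the whole correlation range. The dilution factors follow from averaging four visits and need no correlation assumption.

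**What to change.** - Delete the main-effect gate from Section 2.11.1.
- For each primary outcome, including VAS (the outcome used for sizing), name as the primary test the difference between arms at 3 weeks, adjusted for the baseline value of that outcome, with its 95% CI. Use either ANCOVA or the week-3 contrast of a mixed model with baseline as a covariate and 3 weeks, 6 months and 12 months as responses.
- Report the 6- and 12-month contrasts from the same model as secondary.

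This does not make VAS the sole primary outcome. How several primary outcomes share the error rate is a separate matter.

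The cost is a few sentences. No new data or visits are needed, and the SPSS version already named can run either analysis.
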